#### Verbal Cues for Life Application (Yamas or Niyamas)

Asanas (ie, the physical practice of yoga poses) taught within classes will be infused with verbal teachings of yamas or niyamas (ie, social disciplines to guide relationships with oneself and others) to help cue participants into how yogic philosophies can overflow into everyday life (ie, how to apply skills practiced within class to personal experiences or struggles encountered outside of class). To ensure translatability of the yoga intervention, verbal cues will not explicitly discuss application to WL but will be broad enough so that participants can apply these principles to their weight control practices. Table 1 describes the 5 yamas and 5 niyamas, which simultaneously target several of the self-regulatory mechanisms examined within this study (eg, distress tolerance, mindfulness, and self-compassion). It is also important to note that many weight control behaviors can relate to several yamas and niyamas at once. For instance, choosing to eat and drink in moderation (vs overeating) so that one has more energy to engage in activities that one values can involve brahmacharya (moderation), aparigraha (nongreed), and satya (truth).

**Table 1. T1:** Yamas and niyamas used in yoga.

Practice		Description
Yamas		
	Ahimsa	Nonviolence; making sure not to harm oneself or others; not thinking negative thoughts; kindness and consideration.
	Satya	Truthfulness; being truthful in one’s thoughts, feelings, speech, and actions; being honest with oneself and others.
	Asteya	Nonstealing; not coveting; not being jealous; letting go of cravings. The need to “steal” often arises from a lack of faith in oneself.
	Brahmacharya	Moderation and channeling emotions; having moderation in our actions; conserving energy (slowing down); showing restraint.
	Aparigrapha	Nongreed; nonpossessiveness; greedlessness; simplicity; fulfilling needs rather than wants.
Niyamas		
	Saucha	Purification; cleanliness, internally and externally; purifying the body, mind, and surroundings.
	Santosha	Contentment; detaching from desires to cultivate inner peace.
	Tapas	Self-discipline; using self-discipline to burn out impurities of mind and body.
	Syadhyaha	Self-reflection; the practice of introspection; self-study.
	Ishvara Prandihana	Surrender; surrendering to a higher power.

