##### Dietary Lapses and Potential Lapse Triggers

At each survey, participants will be asked if they ate since the last EMA prompt. If eating was endorsed, a series of questions related to dietary lapse will be asked in addition to questions about potential triggers for lapses. These questions are included in Table 2. When eating is not reported, participants will receive a set of supplemental questions, which do not directly address study aims, to maintain consistency in survey structure and reduce response bias. This approach is consistent with previous work studying dietary lapse [39].

**Table 2. T2:** Summary of ecological momentary assessment variables to be collected.

Variable	Measure	Response options
Dietary lapse		
Dietary lapse (type or total)^a^	Since your last survey (even if it was yesterday), at how many meals or snacks did any of the following occur? (a) Ate past the point of feeling full. (b) Ate a bigger portion than you meant to. (c) Had unplanned eating (ie, ate or drank when you do not usually eat or drink and were not making up for a missed meal). (d) Ate a food that you were intending to avoid or reduce. (e) Went over a calorie goal that you had in mind for yourself.	Number of lapse events
Dietary lapse (frequency)^b^	On the previous question, you indicated that since the last prompt, at least one of the following occurred at XX meals or snacks since the last survey (number from above question will be piped in). Now we want to know at how many meals or snacks did each of the following occur: (1) Ate past the point of feeling full. (2) Ate a bigger portion than you meant to. (3) Had unplanned eating (ie, ate or drank when you do not usually eat or drink and were not making up for a missed meal). (4) Ate a food that you were intending to avoid or reduce. (5) Went over a calorie goal that you had in mind for yourself.	Number of each type of lapse
Potential dietary lapse triggers		
Dietary temptation (type)^c^	Since the last survey (even if it was yesterday), have you experienced any of the following temptations to eat or drink, regardless of whether or not you actually acted on the temptation (check all that apply)?	(a) I was tempted to overeat, (b) I had a sudden urge to eat a tempting food or drink that I have been trying to reduce or avoid, (c) I was exposed to a tempting food or drink, (d) none of the above

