Dietary temptation (details)^d^	If a, b, or c are selected from the question above, the following questions will be asked: (1) thinking about the most recent temptation you had: what was the intensity of the temptation? (2) Did you eat or drink the tempting food or drink?	(1) 1‐7 Likert scale; 1=not at all intense, 7=extremely intense; (2) yes or no
Craving	How strong is your craving to eat a specific food right now?	Visual analog scale: 1=low intensity to 10=high intensity
Momentary affective experience (or related interoceptive state indicators)	(1) Right now, I feel calm, tense, upset, relaxed, content, worried, hungry, stressed, tired, bored, anxious, overwhelmed, ashamed, energetic; and (2) Right now, I feel very good, good, fairly good, neutral, fairly bad, bad, very bad	(1) 5 Likert scale; 1=not at all, 5=extremely; (2) −5 to 5 Likert scale; −5=very bad, +5=very good

a This will be the question used to calculate the total number of lapses.

b This will be the question used to determine the frequency of endorsed types of lapses, if applicable.

c This question will be used to assess the type of dietary temptations.

d These questions will be used to assess the intensity of and ability to resist dietary temptations.

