#### Secondary Aims

Using a similar analytic approach as that described for the primary aim, we will examine intervention effects on secondary outcomes, including frequency of dietary lapses and potential lapse triggers (eg, affect, cravings, and ability to resist dietary temptations), as assessed via EMA. Namely, longitudinal mixed effects models will be specified that regress outcomes over time on intervention group (YOGA vs WELLNESS), time, intervention*time, baseline value of the outcome, and confounders. Models will also adjust for the clustering of data within participants. Effects of day and measurement period will be tested, and adjustments made, as needed.

To evaluate the secondary aims of this study, we will examine potential mediators (eg, affect, mindfulness, self-compassion, and distress tolerance) of the treatment effect on primary (ie, weight change) and secondary outcomes (ie, dietary lapses) using a multiple mediator model with bootstrapped SEs (10,000 bootstrapped samples). Models estimate the path coefficients (a path: effects of YOGA vs WELLNESS on changes from baseline in potential mediators and b path: effects of changes from baseline in potential mediators on WL or lapse outcomes) as well as the indirect effect of intervention (ab path: YOGA vs WELLNESS on outcomes through the mediators).

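### The only item named for ability to resist temptation asks whether the food was eaten, which cannot tell success from failure when the temptation was to overeat

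*Protocol article*

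**What the plan says.** The EMA section on dietary lapses and potential lapse triggers (Protocol article, Table 2) asks which temptations occurred since the last survey. Participants may tick several of three types. The first is about amount: "a) I was tempted to overeat". The second, (b), is an abrupt wish for a particular item that the participant is cutting down on. The third, (c), is having come across something tempting.

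Ticking any of them opens two follow-ups about the most recent temptation: its intensity on a 1 to 7 scale, and a yes/no item, "2) Did you eat or drink the tempting food or drink". Footnote d gives their purpose: "These questions will be used to assess the intensity of and ability to resist dietary temptations". No other item is named for resistance.

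The Secondary Aims paragraph of the analysis plan lists the resulting outcome among those compared between arms: "potential lapse triggers (eg, affect, cravings, and ability to resist dietary temptations". The text introducing Table 2 says that the lapse and trigger questions follow when the participant reports having eaten since the last prompt.

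**The concern.** Types (b) and (c) concern a particular food or drink, so not consuming it is a fair meaning of resisting. Type (a) concerns amount. A person tempted to overeat at a meal resists by stopping, not by eating nothing, and the follow-up does not ask about amount.

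Two features make this worse. On the stated routing, those who reach the item have already reported eating, so yes is the natural answer after (a). And several types may be ticked while the follow-up covers only the most recent temptation, so when (a) is ticked with (b) or (c), the answer cannot be assigned to a type.

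At stake is the interpretation of a named secondary outcome. The Introduction cites less difficulty resisting temptations among the pilot study's yoga participants as part of the rationale, so this contrast will be looked at. The section on verbal cues also illustrates the yoga principles with "choosing to eat and drink in moderation (vs overeating", a kind of success that the resistance item does not register.

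**Working it through.** **Step 1: item against construct.** Taking the item literally, and reading no as resisted:

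| Type ticked | What happened | Truly resisted? | Answer |
|---|---|---|---|
| (a) only | Ate the planned portion, stopped | Yes | Yes |
| (a) only | Overate | No | Yes |
| (b) and/or (c) only | Did not have it | Yes | No |
| (b) and/or (c) only | Had it | No | Yes |
| (a) with (b) or (c) | Either | Depends on which was most recent | Type unknown |

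Rows 3 and 4 separate success from failure. Rows 1 and 2 do not, and no coding of this item alone can make them do so.

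**Step 2: possible size.** The article gives no figure for this outcome, so there is nothing to reproduce. All inputs below are assumptions:

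- true failure to resist, the same for every type: 50% WELLNESS, 40% YOGA (difference 10 points);
- s = share of rated temptations that are type (a), from 0.10 to 0.50;
- m = probability that a type (a) success is answered yes, from 0.5 to 1.0.

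Observed failure = p + s·m·(1 − p). With s and m equal in both arms, the observed difference is (p_W − p_Y)·(1 − s·m).

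| s | m | WELLNESS | YOGA | Difference (points) |
|---|---|---|---|---|
| 0.10 | 0.5 | 52.5% | 43.0% | 9.5 |
| 0.25 | 0.8 | 60.0% | 52.0% | 8.0 |
| 1/3 | 1.0 | 66.7% | 60.0% | 6.7 |
| 0.50 | 1.0 | 75.0% | 70.0% | 5.0 |

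Between 50% and 95% of the true difference is retained, always attenuated.

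**Step 3: unequal type mix.** Keep m = 0.8 and let s differ by arm:

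- s = 0.30 WELLNESS, 0.20 YOGA: (0.50 + 0.30·0.8·0.50) − (0.40 + 0.20·0.8·0.60) = 0.620 − 0.496 = 12.4 points.
- s = 0.20 WELLNESS, 0.30 YOGA: 0.580 − 0.544 = 3.6 points.
- s = 0.15 WELLNESS, 0.40 YOGA: 0.560 − 0.592 = −3.2 points.

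The direction is therefore not fixed. Type mix is measured after randomization and could itself respond to the intervention.

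**The case against.** The strongest reply is that the article prints no scoring rule. It does not say that yes means failure, or that the types are pooled. Type is recorded by a separate question, so an analysis plan that is not shown could exclude (a). That is fair as to the coding, which footnote d implies without stating. It does not answer the mismatch: the footnote assigns this item to resistance after all three types, and for (a) the item does not carry the information.

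A respondent might also read the follow-up as asking whether they gave in (the second helping, say) and answer no after stopping. That would make the misclassification partial, which is why m is allowed to fall to 0.5. It does not make the item unambiguous.

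A reader might infer more than the document supports:

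- *That every temptation episode is scored.* Only the most recent one per survey is rated, and on the stated routing only after reported eating.
- *That the arm contrast must be diluted.* That needs similar type mix and similar responding in both arms; Step 3 shows inflation and reversal otherwise.
- *That a real effect on moderation would go unseen.* The lapse items count meals or snacks at which the participant ate beyond fullness or took more than intended, and dietary lapses are a secondary outcome. The Weight Efficacy Lifestyle Questionnaire also measures confidence in avoiding overeating.
- *That the classes coach against overeating.* The verbal cues are kept free of explicit weight-loss application. The eating example is the authors' illustration, although the twice-monthly texts do link the principles to weight-loss behavior.

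**Conclusion.** The point stands as a mismatch between item and construct in the printed instrument, limited to type (a) prompts and to mixed prompts that include (a). Pooling them with the rest misclassifies resistance. The bias is towards zero if type mix and responding are similar in the two arms, and can go either way if they are not. Its size cannot be stated, because the article gives no type shares; the 5.0 to 9.5 points, and the -3.2 to 12.4 points under unequal mixes, are illustrations against an assumed true difference of 10. They also assume the same true failure rate for every type. One secondary EMA outcome is affected and the primary weight outcome is not, so this deserves correction before analysis but does not threaten the trial's main conclusion.

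**What to change.** Leave the survey as it is: the Results section reports that 4 of 5 cohorts have launched, and changing the item now would split the data. State in the analysis plan:

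1. The resistance outcome uses prompts where only (b) and/or (c) is ticked, with no on the follow-up counted as resisted.
2. The all-prompts version is a sensitivity analysis.
3. The frequency of each temptation type, and resistance by type, are reported for each arm, with a note that yes after (a) alone cannot be read as failure.

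Do not rescore (a) from the lapse items. Those counts cover the whole interval since the last survey and not the most recent temptation, and using them would make a lapse trigger partly the same variable as the lapse outcome. Success in moderating intake is better shown by the fullness and portion-size lapse counts, reported as lapse outcomes.

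The cost is wording and recoding of data already collected. The downside is that fewer prompts contribute and that the subset is selected by a post-randomization response, which is why items 2 and 3 should accompany the main result.

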### Questionnaire Measures

At each assessment, a series of questionnaires will be completed via REDCap. At baseline only, demographic information and food insufficiency will be assessed. Questionnaire measures of self-regulatory mechanisms are found in Table 3 and will be completed at all assessment time points by all participants. At follow-up time points, program satisfaction questionnaires will also be completed, which will be used to assess the acceptability of the IDWL, yoga, and wellness programs. Yoga participants will also be asked to complete several additional questionnaires at follow-up related to their perception of the yoga classes, perceived benefits of practicing yoga [59], and frequency and duration of yoga practice.

**Table 3. T3:** Validated questionnaires administered at baseline, 3-month, 6-month, and 18-month assessments to assess various aspects of self-regulation.

Questionnaire	Assessment	Scoring
Weight Control Strategies [60]	Self-monitoring, exercise, and diet as weight control strategies	0‐90; comprised of a 30-item scale with four component solution for the subscales: (1) dietary choices, (2) self-monitoring strategies, (3) physical activity, and (4) psychological coping
Five Facet Mindfulness Questionnaire [61,62]	Mindfulness (including one’s ability to observe, describe, and act with awareness, and be nonjudgmental and nonreactive to one’s inner experience)	Comprised of 5 subscales: nonjudging (8-40), nonreactivity (7-35), observing (8-40), describing (8-40), and acting with awareness (8-40)
Distress Tolerance Scale [63]	Perceived capacity to tolerate distress	15‐75; higher scores indicate greater distress tolerance
Self-Compassion Scale [64]	Degree to which individuals act compassionate toward themselves when experiencing a difficult time	26‐130; higher scores reflect higher levels of self-compassion
Weight Efficacy Lifestyle Questionnaire [65]	Self-efficacy (one’s confidence in their ability to avoid overeating when faced with certain situations)	20‐100; higher scores indicate greater self-efficacy in managing weight-related behaviors
Behavioral Inhibition System (BIS) and Behavioral Activation System (BAS) [66]	Inhibitory control (measures motivation to avoid aversive outcomes)	BIS: 7‐28; higher BIS scores indicate greater sensitivity to punishment and BAS: 4‐16; higher BAS scores indicate greater sensitivity to reward
Barratt Impulsiveness Scale [67]	Inhibitory control: impulsiveness and includes cognitive, motor, and nonplanning impulsivity	30‐150; higher scores reflect higher impulsivity

### Aerobic PA

Minutes of aerobic PA will be objectively measured for 10 days, at each assessment period, using the previously validated Actigraph accelerometer [68]. Participants will be mailed an accelerometer, provided with instructions on how to wear the device, and be instructed to wear the Actigraph on their waist during all waking hours, except for water-related activities. They will also be asked to keep a log to record when they put the device on, took it off, and any exercise that they may have performed while not wearing the device. When processing the data, only “valid” days (ie, ≥8 hours of Actigraph wear time) will be considered in the analysis. Minutes per day spent in total and bout-related (≥10-minute bouts) moderate-to-vigorous intensity PA will be calculated using validated methods. One common critique of yoga as a WL intervention is that yoga participation may reduce aerobic PA. By objectively assessing PA, this study will be able to empirically answer this question. Upon study completion, at the time of analysis for this study, we will use all recommended processing methods for all accelerometry data and report findings accordingly.

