To date, yoga has largely been overlooked within the context of WL treatment, despite positive effects observed in other health disciplines (eg, cardiovascular disease risk, pain, depression, and smoking cessation) [41-44]. While other disciplines focus on the psychological benefits of yoga, the weight control field has traditionally viewed yoga as a *mode* of exercise (characterized by low energy expenditure and classified as light PA that may not elicit a sufficient caloric deficit to contribute to WL), thereby overlooking the cognitive and emotional pathways through which yoga may enhance WL. Although cross-sectional evidence suggests strong associations between yoga and healthy dietary choices, mindful eating, and emotional eating [25,45-47], studies investigating the inclusion of yoga within WL treatment are limited. A 2021 systematic review that explored relationships between yoga participation and reductions in body weight via decreased energy intake or increased PA identified only 2 prior randomized controlled trials (RCTs), which combined yoga with calorie reduction in individuals with overweight or obesity [48]. The first was a 6-month study conducted among 50 individuals with overweight or obesity and compared 2 styles of yoga, restorative hatha and vinyasa. While this study demonstrated yoga participation within a standard behavioral WL intervention to be feasible, no differences in WL were observed between the 2 styles of yoga, as both groups lost 3.4‐3.8 kg [49]. Further, because it did not have a control condition, any conclusion related to the added effect of yoga on WL is limited. The second study was a 12-week trial conducted in 260 individuals diagnosed with metabolic syndrome and was conducted outside of the United States (India), where yoga practice differs from the United States [50]. Results suggested that a greater proportion of participants randomized to the yoga-based intervention recovered from metabolic syndrome (45.4%) as compared to dietary intervention alone (32.3%). However, energy cost was not controlled for in this study, and observed effects may have been due to elevated PA levels.

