#### Self-Guided Yoga Practice

In addition to participating in the live, virtual classes, participants will also be given a self-guided yoga prescription to assist in the development of their personal practice. To facilitate self-guided practice, participants will be instructed to use video recordings from the study website, which will offer classes from the study’s Iyengar teachers of varying durations (eg, 15, 30, 45, and 60 minutes). The first 3 months will focus more heavily on live yoga instruction, and the last 6 months will be designed to foster a more autonomous practice. The self-guided prescription is based upon total duration (ie, minutes per week) rather than frequency (ie, days per week) to facilitate greater retention and adherence by allowing individuals the choice to practice yoga less frequently for a longer duration (eg, 1 time per week for 60 minutes) or more frequently for shorter durations (eg, 3 times per week; one, 30-minute class and two, 15-minute classes). Progression toward a total dose (ie, combination of live classes and self-guided practice) of 180 minutes per week of yoga practice is the intervention target for both the first 3 months and the final 6 months of the program.

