### Contact Control: Health and Wellness Program

Upon completion of the 3-month assessment visit, participants randomized to WELLNESS will receive a 9-month fully remote, health and wellness program. Similar to YOGA, wellness classes will be approximately 60 minutes in duration and held multiple times per week. Participants will be instructed to attend 2 classes per week for the first 14 weeks and 1 class per week until the 12-month study assessment (22 weeks). Classes will be taught by individuals with a bachelor’s degree or higher in a wellness-related field (eg, nutrition, exercise science, health promotion, and psychology). Classes will consist of lectures, handouts, videos, and discussions addressing a variety of health and lifestyle topics, which include immune health, sleep recommendations, health screenings, healthy aging, vitamins and minerals, and humor and health. WL will not be discussed within these sessions, and participants will be informed that wellness classes are designed to function independently of the IDWL program. Overall, the WELLNESS condition provides a treatment program, which serves as a contact-matched control for the yoga arm.

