## Discussion

### Principal Findings

This paper provides a summary of the rationale and methods of the PATH Trial. The primary goals of this randomized trial are to examine whether the addition of yoga to behavioral WL treatment improves long-term WL and to elucidate mechanisms through which yoga impacts weight in WL-seeking adults. These findings will have clinical relevance, as overweight and obesity are global health challenges linked to cardiometabolic risks, and despite effective WL interventions, long-term WL remains difficult [35,36]. Therefore, it is crucial to identify and test novel strategies, such as yoga, which have the potential to support sustained WL.

This study results from a synthesis of literature from a variety of disciplines using yoga interventions (cardiometabolic, pain, and addiction fields) and proposes a unique application of yoga to the area of weight management. While these other disciplines tend to focus on the psychological benefits of yoga for improving health, the weight control field has traditionally viewed yoga as a “mode” of exercise and has failed to consider that yoga is a mind-body intervention that could indirectly impact weight via psychological mechanisms (eg, improvements in self-regulation). Therefore, it is important to delineate that a yoga practice is not an exercise modality that produces effects similar to aerobic exercise, which has a higher caloric expenditure and is commonly recommended in WL programs, and therefore will be unlikely to elicit a comparable exercise-induced energy deficit [69]. Unlike past literature, this trial is uniquely designed and fully powered to evaluate self-regulatory pathways through which yoga impacts dietary lapses and WL, representing the first RCT to examine these mechanistic pathways within the context of WL treatment.

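### As described, the plan does not account for yoga's energy cost below the moderate-to-vigorous range, so crediting a weight effect to self-regulation is open to the objection it raises against earlier work

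*Protocol article*

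**What the plan says.** All references are to the protocol article.

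- **Criticism of earlier work.** The Introduction discounts a previous yoga trial because "energy cost was not controlled for in this study, and observed effects may have been due to elevated PA levels".
- **Intensity of yoga.** The Introduction reports the weight-control field's traditional view of yoga as exercise: "characterized by low energy expenditure and classified as light PA that may not elicit a sufficient caloric deficit to contribute to WL". The authors think this view overlooks the cognitive and emotional pathways.
- **Yoga dose.** Self-Guided Yoga Practice describes a build-up in live and home practice combined: "180 minutes per week of yoga practice is the intervention target for both the first 3 months and the final 6 months of the program".
- **Control.** Under Contact Control, two classes weekly for 14 weeks, then one weekly for a further 22, at about 60 minutes a class. The content is talks, written material, video and discussion. No movement component and no home practice are stated, and the matching is on contact.
- **Activity measurement.** A waist-worn accelerometer is used during waking hours for 10 days at each assessment. The outputs named are these: "Minutes per day spent in total and bout-related (≥10-minute bouts) moderate-to-vigorous intensity PA will be calculated using validated methods". The stated purpose is to learn whether yoga reduces aerobic activity, and Study Aims lists aerobic exercise as exploratory.
- **Mediators.** The analysis text under Secondary Aims gives "potential mediators (eg, affect, mindfulness, self-compassion, and distress tolerance" as examples. Study Aims adds self-efficacy and inhibitory control. Neither names activity or energy expenditure.
- **Mechanistic claim.** Under Principal Findings the trial is described as "fully powered to evaluate self-regulatory pathways through which yoga impacts dietary lapses and WL".

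**The concern.** Yoga and wellness differ in more than psychological content: one involves movement and the other, as described, does not. If yoga participants lose more weight, part of the difference could come from energy spent in practice. Minutes of moderate-to-vigorous activity would largely miss this if yoga is light activity.

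This matters for the mediation aim. Randomization protects the total effect of yoga on weight and the effect of yoga on each mediator. It does not protect the path from mediator to weight. Within the yoga arm, people who practise more may both expend more energy and score higher on mindfulness, self-compassion or distress tolerance. If activity is left out of the model, some of its contribution can be credited to those scales. If activity did not vary with the scores within an arm, its share would fall into the direct effect instead. The plan as described has no step that would show which is the case.

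At stake is the conclusion that yoga helps weight loss through self-regulation rather than as exercise.

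**Working it through.** The plan states no figure for energy cost, so there is nothing to reproduce. The check has two parts: prescribed time in each arm, from the document, and an illustrative energy cost, from assumed inputs.

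**1. Prescribed time over 36 weeks (14 + 22)**

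- Wellness: (2 × 14) + (1 × 22) = 50 classes × 60 min = 50 h.
- Yoga, minimum live classes: the same 50 h, so live contact is matched.
- Yoga at the combined target: 180 min × 36 weeks = 108 h.
- Practice with no stated counterpart in the control: 108 − 50 = 58 h.

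The 108 h is an upper figure, because the text describes building up to 180 minutes.

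**2. Illustrative energy cost**

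Assumptions, none of them in the document: body weight 90 kg; net cost 0.5 to 2.0 MET above sitting (1 MET taken as 1 kcal/kg/h); 7,700 kcal per kg of weight; no compensation through eating; no displacement of other activity.

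Formula: net MET × kg × hours ÷ 7,700.

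| Yoga time | Net 0.5 MET | Net 1.0 MET | Net 2.0 MET |
|---|---|---|---|
| 108 h (full target) | 4,860 kcal = 0.63 kg | 9,720 kcal = 1.26 kg | 19,440 kcal = 2.52 kg |
| 54 h (half) | 2,430 kcal = 0.32 kg | 4,860 kcal = 0.63 kg | 9,720 kcal = 1.26 kg |
| 36 h (60 min/week) | 1,620 kcal = 0.21 kg | 3,240 kcal = 0.42 kg | 6,480 kcal = 0.84 kg |

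**3. Scale**

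The only between-group weight difference in Sample Size Considerations is 3.5% in median percent weight loss, among pilot participants with high initial loss. For 90 kg this is 0.035 × 90 = 3.15 kg. Body weight cancels in the ratio: share = net MET × hours ÷ (7,700 × 0.035) = net MET × hours ÷ 269.5.

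- Full target: 0.5 × 108 ÷ 269.5 = 20%; 2.0 × 108 ÷ 269.5 = 80%.
- Half: 10% to 40%.
- 60 min/week: 7% to 27%.

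Two cautions apply. The 2.0 MET column is an edge case: if sitting is 1 MET and moderate activity starts at 3 MET (a further assumption), it lies at the boundary, where the planned outputs would begin to register the activity. And 3.5% is a subgroup difference in medians, so these percentages are not estimates for the whole sample; a smaller overall difference would raise them. The table shows only that the pathway cannot be set to zero by assumption.

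**The case against.** The strongest reply is that nothing in the Aerobic PA section is wrong for its purpose. Moderate-to-vigorous minutes are the right output for whether yoga displaces aerobic exercise, and activity is measured objectively in both arms. The section also promises to follow recommended processing for all accelerometer data, so other outputs are not ruled out. The mediator lists are introduced as examples, and one questionnaire in Table 3 has a physical-activity subscale. Final variable lists often sit in a full protocol or analysis plan, which is not shown. Iyengar yoga was chosen partly because it is believed to cost less energy than vigorous styles, and Principal Findings says an energy deficit like that of aerobic exercise is unlikely.

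Much of this stands. A reader might infer that the control is seated, that only moderate-to-vigorous activity can be obtained, and that the trial therefore cannot separate self-regulation from energy expenditure. The document supports none of these. It never says seated; a device worn through waking hours also records lower-intensity movement; and the outputs and mediators named are not closed lists. Light activity is the field's classification as reported, not the authors' own finding. Mediation of dietary lapses is also less exposed, since energy spent does not itself produce a lapse.

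What the reply leaves unanswered is narrower. Choosing a gentler style reduces the energy cost but does not measure it. The comparisons offered are with vigorous yoga and aerobic exercise, whereas the control is a class without stated movement. No listed output or mediator addresses that contrast, although the article makes a strong mechanistic claim and faults another trial on this ground.

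**Conclusion.** The point holds in a limited form. As the article describes it, the plan neither measures nor accounts for yoga's energy cost below the moderate-to-vigorous range. The primary comparison of yoga with wellness on 12-month weight is unaffected, because it is a total effect whatever its route. Only the attribution of a weight effect to self-regulation is open to the Introduction's own criticism.

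The size is uncertain. The 0.63 to 2.52 kg at full dose is an upper bound resting wholly on assumed intensity, body weight and energy conversion, with full adherence and no compensation; realistic values may be well below it. It would be wrong to read the range as showing that activity explains most of any yoga effect.

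This is a cheap improvement to the mechanistic aim, not an error that threatens the trial.

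**What to change.** 1. From the accelerometer data already collected in both arms, also derive light-intensity minutes and total activity volume at 3, 6 and 12 months, and compare the arms on them.
2. Prespecify a sensitivity analysis of the weight mediation model only. Add change in total or light activity and change in moderate-to-vigorous activity as parallel mediators, and report the self-regulation indirect effects with and without them.
3. State that a waist-worn device may under-read static postures, and word the mechanistic conclusion accordingly. Little change after adding activity would be reassuring but not proof.
4. Do not adjust for logged yoga minutes. They exist only in the yoga arm and are in effect treatment dose, so adjusting for them could remove genuine self-regulation effects of the same practice. Use them at most for a descriptive estimate of energy cost over a stated range.

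The cost is analysis time, one or two extra mediators and slightly wider intervals on the indirect effects. No new data collection is needed. The article reports enrollment as ongoing with 4 of 5 cohorts launched, so this can still be fixed before outcome results are known.
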